#### London School of Hygiene & Tropical Medicine – United Kingdom

(<http://www.lshtm.ac.uk/aboutus/introducing/mission/index.htm>)

**Background:** The London School of Hygiene & Tropical Medicine is a world-leading centre for research and postgraduate education in public and global health. The London School is a WHO Collaborating Centre for Trachoma and played a major role in the Global Trachoma

mapping project. They have recently led a study on co-administration of Azithromycin and ivermectin in the Solomon Islands.

**Study Role:** The London School of Hygiene and Tropical Medicine will co-implement this project with AHRI and advise on the study design and implementation of the project.

**International Trachoma Initiative – United States of America (<http://trachoma.org/about-iti>)**

**Background:** The International Trachoma Initiative (ITI) was founded in 1998 in response to the World Health Organization's (WHO) call to eliminate blinding trachoma by 2020 (GET2020). ITI's founding partners, Pfizer and the Edna McConnell Clark Foundation, saw the need for an international nongovernmental organization dedicated solely to the elimination of blinding trachoma. To achieve that goal, ITI collaborates with governmental and nongovernmental agencies at the local, national and international levels to implement the WHO-recommended **SAFE** strategy for trachoma control (**S**urgery; **A**ntibiotics—using donated Zithromax®; **F**acial cleanliness; and **E**nvironmental improvement).

**Study Role:** ITI will provide the funding for all aspects of this study and advice on the study design and implementation.

*NOTE: All of the forms listed below have been adapted together with AHRI based on previous clinical trial reporting forms. It is the desire of the FMOH and study leads to combine these questionnaires into one comprehensive register which, if approved by the in-country ethical review board, will be converted for electronic data capture during the study.*

## Appendix 2: Case recording forms

### Form 1: Recruitment form

**Study Title: Safety of the co-administration of azithromycin, albendazole and ivermectin versus standard treatment regimens during mass drug administration (MDA) in Ethiopia: a cluster-randomized trial**

Name of investigator: ..... Name of supervisor: .....

#### I. Sociodemographic Data

- 1.1. Community ID: |\_\_|\_\_||\_\_|\_\_|\_\_|\_\_|
- 1.2. Participant ID |\_\_|\_\_||\_\_|\_\_|\_\_|\_\_|\_\_|\_\_|
- 1.3. Date of birth |\_\_DD|\_\_MM|\_\_YY|
- 1.4. Approximate age if date of birth is unknown:|\_\_|\_\_|.|\_\_| years
- 1.5. Height :|\_\_|\_\_||\_\_|\_\_|.|\_\_|\_\_| Cms
- 1.6. Sex: 1. Male 2. Female 99. Unknown
- 1.4. Household code.....
- 1.5. Gott: ..... 1.6. Kebele.....
- 1.7. District.....1.8. Region.....
- 1.9. Consent Card Number: |\_\_|\_\_|\_\_|\_\_|
- 1.10. Survey Sheet Number: |\_\_|\_\_|\_\_|\_\_|

#### II. Interview prior to treatment: signs/symptoms or complaint

##### 2.1. Signs and symptoms at presentation: **Tick any as is appropriate:**

| Events prior to treatment |                     | existing prior to treatment |       |
|---------------------------|---------------------|-----------------------------|-------|
| Symptoms/Signs            |                     | 1. Yes                      | 2. No |
| 2.1.1.                    | Fever               |                             |       |
| 2.1.2.                    | Itching/ground itch |                             |       |
| 2.1.3.                    | Headaches           |                             |       |
| 2.1.4                     | Dizziness           |                             |       |
| 2.1.5                     | Tiredness           |                             |       |
| 2.1.6.                    | Deafness            |                             |       |
| 2.1.7.                    | Jaundice            |                             |       |
| 2.1.8.                    | Weakness            |                             |       |

- 2.1.9. Fatigue
- 2.1.10. Nausea
- 2.1.11. Vomiting
- 2.1.12. Diarrhoea
- 2.1.13. Abdominal pain
- 2.1.14. Flatulence/dyspepsia
- 2.1.15. Constipation
- 2.1.16. Joint/muscular pain
- 2.1.17. Swelling of (upper/lower) limbs
- 2.1.18. Swelling of eyelids/abnormal  
feeling in the eyes
- 2.1.19. Rash/plaque
- 2.1.20. Scrotal reaction
- 2.1.21. Skin nodules
- 2.1.22. Worm expulsion
- 2.1.23. Haematuria
- 2.1.24. Lymphoedema
- 2.1.25. Elephantiasis
- 2.1.26. Hydrocele
- 2.1.27. Palpitation/tachycardia
- 2.1.28. Orthostatic hypotension
- 2.1.29. Others
- 2.1.30. **If other specify**..... ..  
..... ..  
..... ..

2.2. ***After completing all Questions under 2.1, the investigator should answer the questions that follows: NB:-the answer will be yes if one complaint is ticked in the above list***

2.2.1. Did the participant have complaints prior to the treatment? 1. Yes 2. No

2.2.1.1. Indicate the **Main complaint**.....

2.2.2. How would you rate this complaint? **1 = minor; 2 = moderate 3=major**

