### 8.4 Recording of any AE/SAEs

The study defines AEs and SAEs per the national guidelines which are also found in the Serious Adverse Events handbook created by RTI ENVISION and the Task Force for Global Health:

**“Adverse event from MDA (AE-F-MDA)** is a medical event that takes place in an MDA program, causes concern in the medical and wider community and is believed to be caused by the drug(s) used. It can be caused by either administration of the drug or by a coincidental event that by chance happened after drug administration. Most AEs-f-MDA (adverse events from MDA) are self-limiting and treatable using simple remedies and are not usually required to be reported to national or international regulatory authorities.

**Serious Adverse Event (SAE)** is a regulatory term describing any untoward medical occurrence with any of the following characteristics:

- Results in death;
- Requires in-patient hospitalization;
- Results in persistent or significant disability;
- Is life-threatening; or
- Results in a congenital anomaly/birth defect.”

All adverse events will be recorded and followed up by the nurses on the team. The reporting of adverse events will be systematic and comply with national AE/SAE reporting guidelines to avoid any bias related to the wording of the question(s).

While the difference between “adverse events” and “serious adverse events” have been described above, there is also a level of severity which the study will also monitor: “The term “severe” is often used to describe the intensity (severity) of a medical event, as in the grading “mild”, “moderate”, and “severe”; thus a severe action need not be serious.” Reported adverse events will be classified according to their intensity (none, mild, moderate, and severe).

- Mild: easily tolerated, does not interfere with daily activity,

- Moderate: uncomfortable enough to interfere with daily activity,
- Severe: precludes daily activity (Given that a “severe” adverse event includes inability to complete daily activities, it will be classified as a possible SAE for the purposes of this study.)

The evolution of older complaints will be classified as: exacerbated, ongoing, and improved or resolved/none.

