The causal relationship of serious adverse events observed with the triple therapy will be assessed as: *Unrelated, Unlikely, Likely*. The study will utilize information collected by the clinical nurses using the “Conduct an AE Investigation” steps detailed in the Serious Adverse Event Handbook. It is important to note that the study will not follow-up “minor” or “moderate” adverse events up with the full investigative checklist prescribed by the handbook but will reserve this for “severe” adverse events and SAEs. The PI, supervisors, and independent monitors will meet to review these determinations. If the supervisory group questions the results of the clinical nurses’s investigations, it will perform its own investigation of the report as an addendum to the original report. Incidences will be analysed based on preferred terms and body system levels. “Severe” adverse events and SAEs occurring during exposures will be analysed based on 3 levels of selection per pre-existence and causality:

- Treatment emergent signs and symptoms (TESS), i.e., all AE during exposure to treatment or that were not pre-existing
- TESS without causality ‘unlikely’
- TESS with causality ‘likely’

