| 4.1.8.1.10                           | Nausea              |                                |       |
| 4.1.8.1.11                           | Vomiting            |                                |       |
| 4.1.8.1.12                           | Diarrhoea           |                                |       |
| 4.1.8.1.13                           | Abdominal pain      |                                |       |

- 4.1.8.1.14 Flatulence/dyspepsia
- 4.1.8.1.15 Constipation
- 4.1.8.1.16 Joint/muscular pain
- 4.1.8.1.17 Swelling of (upper/lower) limbs
- 4.1.8.1.18 Swelling of eyelids/abnormal feeling in the eyes
- 4.1.8.1.19 Rash/plaque
- 4.1.8.1.20 Scrotal reaction
- 4.1.8.1.21 Skin nodules
- 4.1.8.1.22 Worm expulsion
- 4.1.8.1.23 Haematuria
- 4.1.8.1.24 Lymphoedema
- 4.1.8.1.25 Elephantiasis
- 4.1.8.1.26 Hydrocele
- 4.1.8.1.27 Palpitation/tachycardia
- 4.1.8.1.28 Orthostatic hypotension
- 4.1.8.1.29 Others
- 4.1.8.1.30 **If other specify**.....
- .....
- .....

3.2.7.2. Did the respondent experience complaints after taking the 3 drugs? 1. Yes 2. No  
99. unknown

3.2.7.3. If yes, which one(s)? (See questions under 4.1.8.1).....  
.....  
.....

**3.2.7.4.** How would you qualify your main complaint (see questions under 4.1.8.2), after taking the 3 drugs **1 = Improved 2 = Ongoing 3 = Exacerbated 4= Resolved**

3.2.7.5. If the respondent says **Bad (worsened than before treatment) for 4.1.8**, review questions under 2.1 “**For complaints or events to prior to the treatment**” to describe **their evolution**. Use the coding; 0 = **did not feel sick**, 1=**mild**, 2 = **Moderate**, 3 = **Major/severe**; to grade them as in the list below

3.2.7.6.

| Adverse event due to worsened existing symptoms before treatment |                                    |            |      |
|------------------------------------------------------------------|------------------------------------|------------|------|
| Symptoms/signs                                                   | when did the side effects appeared | Evaluation | Code |

|            |                                                  | D1 | D2 | D3 | D4 | D5 | D8 | D2 | D8 |
|------------|--------------------------------------------------|----|----|----|----|----|----|----|----|
| 4.1.8.5.1  | Fever                                            |    |    |    |    |    |    |    |    |
| 4.1.8.5.2  | Itching/ground itch                              |    |    |    |    |    |    |    |    |

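### Ticked symptoms other than the main complaint get no baseline grade, yet people who feel bad at follow-up have them graded in absolute terms under a heading that calls them worsened

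*Protocol*

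**What the plan says.** **Before treatment (Appendix 2, Form 1).** Item 2.1 lists 28 named symptoms plus an Others line. Each is ticked Yes or No under the heading "existing prior to treatment", with no severity column. Item 2.2.1 asks "Did the participant have complaints prior to the treatment", and one main complaint is written down. Item 2.2.2 rates that complaint alone: "How would you rate this complaint", coded "1 = minor; 2 = moderate 3=major". The form does not define these labels.

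**Rule in the text (section 8.4).** "Reported adverse events will be classified according to their intensity (none, mild, moderate, and severe"), with mild, moderate and severe defined by interference with daily activity. For complaints already present the rule is different: "The evolution of older complaints will be classified as: exacerbated, ongoing, and improved or resolved/none".

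**At follow-up (Appendix 4).** Item 3.2.7 asks how the person felt after the drugs.
- Those who felt fine go to 3.2.7.1, which gives each pre-existing symptom a change code (none, improved, ongoing, exacerbated).
- Those who felt bad go to 3.2.7.5 and 3.2.7.6. There the pre-existing symptoms are coded 0 to 3, from not feeling sick to major/severe, in a table headed "Adverse event due to worsened existing symptoms before treatment".
- Those who felt the same are sent to neither.

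**The concern.** A symptom present before dosing is an adverse event of treatment only if it got worse. To judge that, the record needs either a grade before and after on one scale, or a change code for each symptom. For people who feel bad, the group in which worsening matters most, the forms give neither for any ticked symptom beyond the main complaint.

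Two things are at stake. The first is the primary outcome, the incidence of AEs and SAEs, because entries in the worsened-symptom table are labelled adverse events. The second is the safety route. A note under that table sends any severe entry to the SAE form, section 8.4 treats a severe event as a possible SAE, and section 8.5 has an SAE trigger a call with the DSMB. The symptom list includes long-standing conditions such as deafness, lymphoedema, elephantiasis and hydrocele, in a woreda chosen partly because LF is endemic there.

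A later analysis plan cannot repair this, because a grade not taken before dosing cannot be recovered.

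**Working it through.** The plan gives no figure to reproduce, so the check sets the forms side by side.

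**Step 1: what baseline exists for each symptom.**

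| Status on Form 1 | Baseline severity on record | Can worsening be checked? |
|---|---|---|
| Ticked No | None (the bottom of the 8.4 scale) | Yes: any later grade is new |
| Ticked Yes, main complaint | Minor, moderate or major, undefined | Roughly, if the labels are read as mild, moderate, severe |
| Ticked Yes, not the main complaint | Nothing beyond the tick | No |

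If a person ticks k symptoms, the number without a baseline grade is 0 when k = 0 and k − 1 when k ≥ 1. One tick gives 1 − 1 = 0; two give 2 − 1 = 1; four give 4 − 1 = 3. The gap therefore lies in people with two or more complaints before treatment.

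**Step 2: what follow-up records for a pre-existing symptom.**

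| Answer to item 3.2.7 | Per-symptom record | Agrees with the 8.4 evolution rule? |
|---|---|---|
| Fine | Change code (3.2.7.1) | Yes |
| Same as before | No symptom review specified | No |
| Bad | Absolute code 0 to 3 (3.2.7.5, 3.2.7.6) | No |

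Item 3.2.7.5 tells staff to describe the evolution of the earlier complaints but supplies intensity codes. An intensity set against a Yes tick does not show change. Item 3.2.7.4 has a change code, but only for one main complaint.

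**Step 3: follow one case.** Suppose a person ticks headache (main complaint) and joint pain, and the joint pain already prevents daily activity. The next day the person has new nausea and answers bad. Staff return to the ticked symptoms, and the joint pain is coded 3. Under 8.4 it is ongoing. On the form it stands under a heading for worsened symptoms and goes on to the SAE form. A person whose joint pain went from mild to severe would leave the same record, so nothing on paper separates the two.

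**The case against.** The strongest reply is that worsening is captured directly. Section 8.4 requires an evolution category, 3.2.7.1 defines its codes against the state before treatment, and the graded table is meant for people who are worse. A careful nurse would leave an unchanged symptom out of it. The first active visit is the day after dosing, so recall is short. This shows the intent is sound, but the answer bad describes the person and not each symptom, and the instruction sends staff through all earlier complaints. The conflict with 8.4 stands.

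Three further points are right and limit the concern.
- A No tick is a baseline of none. A reader might infer from the 29 symptom lines and single rating that 28 of 29 have no baseline. The form does not support that; only ticked symptoms beyond the main complaint are affected.
- The labels are loosely aligned. Item 3.2.7.5 writes major/severe as one code, and section 8.5 uses minor where 8.4 uses mild. The scale on Form 1 is undefined rather than demonstrably different.
- A reader might infer that a symptom going from mild to severe would be set aside as pre-existing in the section 8.5 selection of severe events. Its first level reads "all AE during exposure to treatment or that were not pre-existing", and the word *or* does not exclude such an event. That selection rests mainly on the Yes/No tick, which is recorded.

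It is also fair that the note before Appendix 2 treats the forms as provisional, to be merged into one register and converted for electronic capture. That makes the change easy to place; it does not make it unnecessary.

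**Conclusion.** The defect holds within limits. For people with two or more complaints before treatment, every ticked symptom but one lacks a baseline grade. For people who feel bad, the forms depart from the section 8.4 rule, and for people who feel the same they give no symptom review. An unchanged symptom can be recorded as a worsened or severe adverse event, and the record cannot show otherwise.

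The size cannot be derived, because the documents give neither the rate of complaints before treatment nor any rate of misjudgement. A reader might infer that the fault could use up the whole margin. That margin is 0.015 × 8,000 = 120 people per arm, or 0.015 × 6,840 = 102.6. If 10%, 20% or 30% had a complaint beforehand, 120 would be 120/800 = 15%, 120/1,600 = 7.5% or 120/2,400 = 5% of them. These rates are assumptions, and the sum needs a net error of that size in one arm and one direction, beyond any in the other. Nothing in the documents points to that: one set of forms is shown and each arm has an independent monitor. The arithmetic is not evidence of bias of that order.

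This is a worthwhile, inexpensive correction to the forms. It does not affect the sample size and is not in itself a threat to the trial's conclusion.

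**What to change.** 1. In Form 1 item 2.1, record the section 8.4 grade (mild, moderate, severe) for each symptom ticked Yes. Use the same labels in items 2.2.2 and 3.2.7.5.
2. In Appendix 4, apply the section 8.4 evolution code to every pre-existing symptom for all respondents, whatever they answer to item 3.2.7.
3. State in section 8.4 or 8.9 that a pre-existing symptom counts as an adverse event when its grade rises above the recorded baseline or when it is coded exacerbated, and does not count when it is ongoing at the same grade.

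The exacerbated limb in step 3 is needed. A rule based on the grade alone would drop worsening within a grade and any worsening from a severe baseline. In a non-inferiority comparison of adverse events, such losses could favour non-inferiority.

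Cost: a few extra seconds for people who report a symptom, one more field in the ODK form, and a sentence in the protocol. The planned merging of the forms is the natural time to do it.

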2.2.3. Is volunteer eligible for the study? 1 Yes 2 No 99 Unknown

2.2.4. Is informed consent/assent obtained? 1 Yes 2 No 99 unknown

*Thank her/him for volunteering and accompany him/her to the treatment station with his/her file*

### Appendix 3: Treatment form

#### 2.1 Sociodemographic data

2.2 Community ID: |\_\_|\_|\_|\_|\_|\_|\_|\_|\_|\_|\_|

2.3 Participant ID |\_\_|\_|\_|\_|\_|\_|\_|\_|\_|\_|\_|\_|\_|\_|\_|

2.1.3. Date of birth |\_\_|\_|\_|\_|\_|\_|\_|\_|\_|\_|\_|

2.1.4. Approximate age if date of birth is unknown: |\_\_|\_|\_|\_|\_| years

2.1.5. Sex: 1. Male 2. Female 99. Unknown

2.1.6. Household code.....

2.1.7. Gott: ..... 2.1.8. Kebele.....

2.1.9. District..... 2.1.10.

Region.....

2.1.11. Height: |\_\_|\_|\_|\_|\_|\_|\_|\_|\_| CM

2.1.12. Weight: |\_\_|\_|\_|\_|\_| kg

2.1.13. Number of tablets taken:

2.1.14. IVM: |\_\_|\_|

2.1.15. ZI: |\_\_|\_|

2.1.16. ALB: |\_\_|\_|

2.1.17. Date of DOT co-administration |\_\_|\_|\_|\_|\_|\_|\_|\_|\_|\_|\_|

2.1.18. Time of DOT co-administration |\_\_|\_|\_|\_|\_|\_|\_|\_|\_| hrs

#### 2.2. Implementing physician/health professional directed information

2.2.11. Did the participant swallow the three drugs in your presence? 1. Yes 2. No

2.2.12. Did the participant regurgitate the drugs? 1. Yes 2. No

2.2.13. Were the drugs taken again after regurgitating? 1. Yes 2. No

2.2.14. Was the treatment validated? 1. Yes 2. No

(Thank the subject for his participation and keep his file for surveillance)

## Appendix 4: AES Surveillance form

- 3.1. Community ID: |\_\_|\_|\_|\_|\_|\_|\_|\_|\_|\_|\_|
- 3.2. Participant ID |\_\_|\_|\_|\_|\_|\_|\_|\_|\_|\_|\_|
- 3.2.1. Dates of first filling-in for surveillance purposes |\_\_DD|\_\_MM|\_\_YY|
- 3.2.1.1. Which day(s), please underline D1, D2, D3, D4, D5, D6, D7, D8, D9, D10, D11, D12, D13, D14, D15, D16, D17, D18, D19, D20, D21, D22, D23, D25, D26, D27, D28, D29, D20
- 3.2.2. Place of first filling-in? 1. Survey site 2. Home 3. Other 99. unknown
- 3.2.3. If other in 4.1.2., specify the place.....
- 3.2.4. Did you take all the three drugs? 1. Yes 2. No 99. unknown
- 3.2.5. Did you regurgitate the drugs? 1. Yes 2. No 99. Unknown
- 3.2.6. When did you take the drugs? |\_\_DD|\_\_MM|\_\_YY|
- 3.2.7. How did you feel after taking the drugs? 1. Fine (better than before) 2. Same as before 3. Bad 98. Do not know
- 3.2.7.1. If the respondent says **fine (better than before)** for 4.1.8, review questions under 2.1 “**For complaints or events prior to the treatment**” to describe their evolution. Use the coding; 0 = **None**: the complaint has gone, 1=**Improved**: the complaint is significantly less than before the treatment, 2 = **Ongoing**: the complaint is the same as before the treatment, 3 = **Exacerbated**: the complaint increased after the treatment; to grade them as in the list below

| Events existing before the treatment |                     | complaints (tick as necessary) | Grade |
|--------------------------------------|---------------------|--------------------------------|-------|
| 4.1.8.1.1                            | Fever               |                                |       |
| 4.1.8.1.2                            | Itching/ground itch |                                |       |
| 4.1.8.1.3                            | Headaches           |                                |       |
| 4.1.8.1.4                            | Dizziness           |                                |       |
| 4.1.8.1.5                            | Tiredness           |                                |       |
| 4.1.8.1.6                            | Deafness            |                                |       |
| 4.1.8.1.7                            | Jaundice            |                                |       |
| 4.1.8.1.8                            | Weakness            |                                |       |
| 4.1.8.1.9                            | Fatigue             |                                |       |
| 4.1.8.1.10                           | Nausea              |                                |       |
| 4.1.8.1.11                           | Vomiting            |                                |       |
| 4.1.8.1.12                           | Diarrhoea           |                                |       |
| 4.1.8.1.13                           | Abdominal pain      |                                |       |

- 4.1.8.1.14 Flatulence/dyspepsia
- 4.1.8.1.15 Constipation
- 4.1.8.1.16 Joint/muscular pain
- 4.1.8.1.17 Swelling of (upper/lower) limbs
- 4.1.8.1.18 Swelling of eyelids/abnormal feeling in the eyes
- 4.1.8.1.19 Rash/plaque
- 4.1.8.1.20 Scrotal reaction
- 4.1.8.1.21 Skin nodules
- 4.1.8.1.22 Worm expulsion
- 4.1.8.1.23 Haematuria
- 4.1.8.1.24 Lymphoedema
- 4.1.8.1.25 Elephantiasis
- 4.1.8.1.26 Hydrocele
- 4.1.8.1.27 Palpitation/tachycardia
- 4.1.8.1.28 Orthostatic hypotension
- 4.1.8.1.29 Others
- 4.1.8.1.30 **If other specify**.....
- .....
- .....

3.2.7.2. Did the respondent experience complaints after taking the 3 drugs? 1. Yes 2. No  
99. unknown

3.2.7.3. If yes, which one(s)? (See questions under 4.1.8.1).....  
.....  
.....

**3.2.7.4.** How would you qualify your main complaint (see questions under 4.1.8.2), after taking the 3 drugs **1 = Improved 2 = Ongoing 3 = Exacerbated 4= Resolved**

3.2.7.5. If the respondent says **Bad (worsened than before treatment) for 4.1.8**, review questions under 2.1 “**For complaints or events to prior to the treatment**” to describe **their evolution**. Use the coding; 0 = **did not feel sick**, 1=**mild**, 2 = **Moderate**, 3 = **Major/severe**; to grade them as in the list below

3.2.7.6.

| Adverse event due to worsened existing symptoms before treatment |                                    |            |      |
|------------------------------------------------------------------|------------------------------------|------------|------|
| Symptoms/signs                                                   | when did the side effects appeared | Evaluation | Code |

|            |                                                  | D1 | D2 | D3 | D4 | D5 | D8 | D2 | D8 |
|------------|--------------------------------------------------|----|----|----|----|----|----|----|----|
| 4.1.8.5.1  | Fever                                            |    |    |    |    |    |    |    |    |
| 4.1.8.5.2  | Itching/ground itch                              |    |    |    |    |    |    |    |    |
| 4.1.8.5.3  | Headaches                                        |    |    |    |    |    |    |    |    |
| 4.1.8.5.4  | Dizziness                                        |    |    |    |    |    |    |    |    |
| 4.1.8.5.5  | Tiredness                                        |    |    |    |    |    |    |    |    |
| 4.1.8.5.6  | Deafness                                         |    |    |    |    |    |    |    |    |
| 4.1.8.5.7  | Jaundice                                         |    |    |    |    |    |    |    |    |
| 4.1.8.5.8  | Weakness                                         |    |    |    |    |    |    |    |    |
| 4.1.8.5.9  | Fatigue                                          |    |    |    |    |    |    |    |    |
| 4.1.8.5.10 | Nausea                                           |    |    |    |    |    |    |    |    |
| 4.1.8.5.11 | Vomiting                                         |    |    |    |    |    |    |    |    |
| 4.1.8.5.12 | Diarrhoea                                        |    |    |    |    |    |    |    |    |
| 4.1.8.5.13 | Abdominal pain                                   |    |    |    |    |    |    |    |    |
| 4.1.8.5.14 | Flatulence/dyspepsia                             |    |    |    |    |    |    |    |    |
| 4.1.8.2.15 | Constipation                                     |    |    |    |    |    |    |    |    |
| 4.1.8.5.16 | Joint/muscular pain                              |    |    |    |    |    |    |    |    |
| 4.1.8.5.17 | Swelling of (upper/lower) limbs                  |    |    |    |    |    |    |    |    |
| 4.1.8.5.18 | Swelling of eyelids/abnormal feeling in the eyes |    |    |    |    |    |    |    |    |
| 4.1.8.5.19 | Rash/plaque                                      |    |    |    |    |    |    |    |    |
| 4.1.8.5.20 | Scrotal reaction                                 |    |    |    |    |    |    |    |    |
| 4.1.8.5.21 | Skin nodules                                     |    |    |    |    |    |    |    |    |
| 4.1.8.5.22 | Worm expulsion                                   |    |    |    |    |    |    |    |    |
| 4.1.8.5.23 | Haematuria                                       |    |    |    |    |    |    |    |    |
| 4.1.8.5.24 | Lymphoedema                                      |    |    |    |    |    |    |    |    |
| 4.1.8.5.25 | Elephantiasis                                    |    |    |    |    |    |    |    |    |
| 4.1.8.5.26 | Hydrocele                                        |    |    |    |    |    |    |    |    |
| 4.1.8.5.27 | Palpitation/tachycardia                          |    |    |    |    |    |    |    |    |
| 4.1.8.5.28 | Orthostatic hypotension                          |    |    |    |    |    |    |    |    |
| 4.1.8.5.29 | Others                                           |    |    |    |    |    |    |    |    |
| 4.1.8.5.30 | If other specify.....                            |    |    |    |    |    |    |    |    |
|            | .....                                            |    |    |    |    |    |    |    |    |

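### The Appendix 4 surveillance form does not deliver the section 8.4 classification of older complaints, so unchanged and worsened ones cannot be reliably told apart

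*Protocol*

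**What the plan says.** Protocol section 8.4 states the rule for complaints present before treatment: "The evolution of older complaints will be classified as: exacerbated, ongoing, and improved or resolved/none". It attaches no condition to the person's overall feeling.

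Before treatment, Appendix 2 (Form 1, item 2.1) ticks each listed symptom yes or no. The investigator then names one main complaint, and item 2.2.2 asks "How would you rate this complaint" with the labels minor, moderate and major. No other baseline complaint is rated.

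After treatment, Appendix 4 item 3.2.7 asks "How did you feel after taking the drugs? 1. Fine (better than before) 2. Same as before 3. Bad 98. Do not know". The items that follow are:

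- **3.2.7.1**, for 'Fine': each earlier complaint is coded none, improved, ongoing or exacerbated. The last code is explained as "the complaint increased after the treatment; to grade them as in the list below".
- **3.2.7.2 and 3.2.7.3**, no condition: "Did the respondent experience complaints after taking the 3 drugs? 1. Yes 2. No", then which ones.
- **3.2.7.4**, no condition: "How would you qualify your main complaint (see questions under 4.1.8.2), after taking the 3 drugs", with the codes "1 = Improved 2 = Ongoing 3 = Exacerbated 4= Resolved".
- **3.2.7.5 and 3.2.7.6**, for 'Bad': earlier complaints are reviewed for their evolution, but the codes are did not feel sick, mild, moderate and major/severe. The table is headed "Adverse event due to worsened existing symptoms before treatment".
- **3.3**, no condition: a grid of AEs after the drugs, with the same symptom list, the day of appearance and a mild/moderate/severe code.

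The primary outcome (section 10) is the incidence of AEs and SAEs over one month, compared between arms. The non-inferiority margin is 1.5 percentage points (sections 8.1 and 8.9).

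**The concern.** In a community with background symptoms, an AE proportion depends on separating three states: a new symptom, an old symptom that worsened, and an old symptom that merely persists. Section 8.4 provides the classification for the last two. If the form does not collect it for everyone, two errors become possible. A persisting complaint may be recorded as an AE, and a real exacerbation may not be recognisable as one.

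The symptom list includes conditions that can be long-standing, such as lymphoedema, hydrocele, elephantiasis and deafness, and the woreda was chosen partly because LF is endemic there. The same record feeds the comparison of mild and moderate AEs that triggers a DSMB teleconference (section 8.5 and Appendix 10). Evolution that was never recorded cannot be supplied by an analysis plan.

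**Working it through.** No figure in the protocol turns on this item, so the check sets the form against section 8.4. The form's internal references are shifted (4.1.8 stands for 3.2.7, and so on); I read this as a numbering slip.

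**What each overall answer yields for an older complaint**

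| Answer to 3.2.7 | Evolution code for each complaint | Other places it can appear |
|---|---|---|
| Fine | Yes, all four codes | 3.2.7.2 to 3.2.7.4, grid 3.3 |
| Same as before | None | 3.2.7.2 to 3.2.7.4, grid 3.3 |
| Bad | None; severity only, under a 'worsened' heading | 3.2.7.2 to 3.2.7.4, grid 3.3 |
| Do not know | None | 3.2.7.2 to 3.2.7.4, grid 3.3 |

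Section 8.4 requires the middle column to be filled in every row. It is filled in one.

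**Three illustrative records**

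1. *Mild headache before, unchanged after; the person answers 'Bad' because of vomiting.* The nurse must review the headache. Grading it mild is truthful, but places it in the table for worsened symptoms. Leaving it blank is possible, but no instruction says to do so.
2. *Joint pain has worsened; the person answers 'Same'.* There is no review. The pain can be named in 3.2.7.3, coded in 3.2.7.4 if it is the main complaint, and entered in 3.3. An entry in 3.3 does not show whether the pain worsened or persisted.
3. *Headache gone, abdominal pain worse; the person answers 'Fine'.* The pain is coded exacerbated in 3.2.7.1, which takes neither onset nor severity. Grid 3.3 can take both.

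**Can the gap be closed at analysis?**

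- Form 1 item 2.1 flags which symptoms pre-existed. Excluding all of them discards true exacerbations; keeping all of them counts persisting complaints.
- Comparing severity before and after is possible only for the main baseline complaint, and the two scales use different labels. By its cross-reference, the main complaint in 3.2.7.4 is the one reported after the drugs, which need not be the one rated at baseline.
- The selection on pre-existence in section 8.5 (treatment-emergent signs and symptoms) is stated for severe AEs and SAEs. It is not stated for mild or moderate ones.

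**Effect of a false-AE rate common to both arms**

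Suppose a fraction f of people without a true AE is counted as having one, equally in both arms. The observed proportion is p + (1 − p)f, so the observed difference is (1 − f) times the true difference. With true rates of 7% and 8.5% (the protocol's planning figures) the true difference is 1.5 points. Taking f from 0.5% to 3%, an assumption with no source in the documents:

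- f = 0.5%: 1.5 × 0.995 = 1.49 points
- f = 3%: 1.5 × 0.97 = 1.46 points

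A common shift therefore raises the level in both arms but hardly changes the difference.

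**The case against.** The other side has good points, and several of them stand.

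- **The exacerbated code is not confined to people who feel better.** Item 3.2.7.4 offers it without a condition. This stands, but it covers one complaint per person.
- **People who answer 'Same' are not skipped altogether.** Items 3.2.7.2 to 3.2.7.4 and grid 3.3 remain open to them. This stands: records 2 and 3 above are possible losses, not certain ones.
- **The 'Bad' branch concerns worsening.** Item 3.2.7.5 glosses the answer as worse than before treatment, and the table heading says the same, so a careful nurse might omit an unchanged complaint. This stands as mitigation. However, the gate is an overall feeling, while the review covers each complaint.
- **The protocol does not say which tables feed the primary proportion.** This stands; the mapping may properly be in the analysis plan. A reader might infer that the primary record will be misclassified. The documents support only a risk of it.
- **The forms are not final.** The note closing Appendix 1 foresees merging them into one register, and section 8.9 foresees ODK conversion. That argues for correcting them at that step.

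Two stronger readings of the size are tempting. One is that false AEs could exceed the 1.5-point margin. That sets a level common to both arms against a margin on the difference, and the arithmetic above shows little dilution. The other is a bias towards non-inferiority because section 8.8 runs the process twice in the control arm. If miscoding were independent in each round, f in the control arm would become 1 − (1 − f)². A true 1.5-point excess would then appear as 1.03 points at f = 0.5%, or 0.56 at 1%. If the same people were miscoded in both rounds, the shift would largely disappear. The documents give neither f nor the dependence, so neither reading is established.

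**Conclusion.** The point holds as a mismatch between section 8.4 and Appendix 4. Complaint-by-complaint evolution is collected after one of four overall answers. The 'Bad' branch has no code for unchanged or improved. The ungated items do not fill the gap for complaints other than the main one. Baseline severity is too sparse to rebuild worsening afterwards.

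The consequence is a risk of error in both directions in the record behind the primary AE proportion. Its size cannot be derived: the documents give no prevalence of baseline complaints, no distribution of answers to 3.2.7 and no rule for handling unchanged complaints. The conclusion rests on reading the shifted item numbers as a slip and the unconditioned items as open to everyone. It is worth correcting because the missing information cannot be recovered once the interviews are done.

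**What to change.** In Appendix 4, separate the evolution review from the answer to 3.2.7:

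1. For every complaint ticked in Form 1 item 2.1, ask the evolution code (none, improved, ongoing, exacerbated), whatever the overall answer.
2. Take onset day and severity for those coded exacerbated.
3. State that a pre-existing complaint counts as an AE only when it is coded exacerbated. The protocol does not now say when an older complaint counts, so this is an added definition. It agrees with the existing table heading, which treats worsened symptoms as AEs.

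The cost is form wording and skip logic before ODK conversion, plus slightly longer interviews for people with baseline complaints. No extra visit or staff is needed.
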